We also developed the following secondary hypotheses:H4–7) Compared to the control group, the intervention group will report significantly lower scores in terms of conduct problems (H4), hyperactivity/inattention (H5), and peer relationship problems (H6), and higher levels of prosocial behavior (H7) at T3.H8) The intervention group will report significantly higher levels of quality of life than the control group at T3.H9–11) The intervention group will report significantly less frequent headache, abdominal pain, and nausea (H9), less body image dissatisfaction (H10), and fewer sleep problems (H11) than the control group at T3.H12–14) Compared to the control group, the intervention group will report significantly higher scores in terms of frequency of communicating needs (H12), setting boundaries (H13), and connecting with adults (H14) at T3.H15) The intervention group will report significantly less school non-attendance than the control group (H15) at T3.

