The Quality of My Life Questionnaire (QoML; Gong et al., 2007) is used to assess quality of life (QoL). The questionnaire consists of three items: two visual analog scales (VAS) and a categorical measure of change in QoL. The QoML asks “Overall, my life is . . .”. Participants record their responses on a digital VAS for each question stem, which ranges from “the worst” (0) to “the best” (100), with higher scores suggesting better QoL. The questions are only completed by children aged 11 to 17. The QoML serves as a secondary outcome (Hypothesis 8). Previous research established convergent validity in a sample of children living with a chronic health condition (Gong et al., 2007) but the scale has not been validated within a Danish sample.

Physical health is assessed across three domains: somatization, body size perceptions, and sleep quality. Somatization is indicated by one question from the Strength and Difficulties questionnaires, which assesses whether children experience headaches, stomach aches, or nausea (item 3 of the SDQ). This item has previously been used in a national cohort investigation of children's well-being in Denmark (Ottosen et al., 2022). We assessed perceptions of body size, with responses ranging from “much too thin” (1) to “much too fat” (5). This item was drawn from The Health Behaviour in School-aged Children (HBSC) study (Currie et al., 2014), to reflect body image dissatisfaction, a potential predictor of physical and mental health (Currie et al., 2014). Sleep quality is assessed by asking whether the child has had difficulties falling asleep during the last month. This item was also drawn from the HBSC study (Currie et al., 2014, section 5.10). Participants are provided with the following response options: “never” (1), “a couple of times” (2), “almost every week” (3), “more than once a week” (4), and “almost every day” (5). These three items serve separately as secondary outcomes (Hypothesis 9–11). Of note, Denmark is a participating member of the The Health Behaviour in School-aged Children (HBSC) study and thus, the items have been employed in national surveys of school-aged children, aged 11, 13, and 15 years (Madsen et al., 2023).

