School non-attendance is measured with one item that examines whether and how many days the child has been absent from school or day care, over the last 4 weeks (for T1 and the T2) or 8 weeks (for T3). Participants respond with the number of days, ranging from 0 to 20 days for T1 and the T2 (i.e., 4-week school- or daycare-period), and 0 to 40 for the T3 (i.e., 8-week school- or daycare-period). Participants are also able to respond that they do not know or that the question is not relevant to them (in cases of vacations or the child not attending school/daycare). The item for school non-attendance follows the construct guidelines proposed by Heyne et al. (2020). A percentage will be calculated for full days of absence, such that higher percentages indicate higher school non-attendance; this variable serves as a secondary outcome (Hypothesis 15).

Degree of conflict is reported by parents and youths (11 to 17 years) using the 6-item self-report Divorce Conflict Scale, developed and validated within a Danish sample (DCS; Hald et al., 2020b). Participants respond to the items using a 4 to 6-point rating scale (response options vary by item stem). Items are summed together to create a score that can range from 0 to 27, such that higher scores indicate greater conflict. This variable serves as an exploratory outcome, as we expect that parents may reduce their conflict in response to 1) exposure to the content of the child intervention and 2) because the child fares better, as child well-being and co-parenting can be a point of conflict for parents (e.g., Johnston, 1994; Hald et al., 2020b).

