### Statistical analyses

1.6

Due to the nesting of participants within family units, all analyses are conducted within a multilevel modelling framework, accounting for the interdependence in the data (children nested within parent). Attrition bias analyses will be conducted, comparing participants who only completed T1 to those who remained in the study after T1 (i.e. completed T2 and/or T3 assessment), using multilevel logistic regression, with drop-out as the outcome and baseline sociodemographic and psychological variables as predictors.

To examine the effectiveness of the intervention, multilevel regressions will be conducted to examine group differences on the primary outcomes: SDQ-Emotional (H1), SDQ-Total (H2), and SDQ-Impact (H3) at T3. These analyses will be based on the intention-to-treat principle (Gupta, 2011). Multiple imputations using chained equations as implemented in the R package mice will be applied to handle missing data. The regression models will be specified to allow for a random intercept, as well as for interdependence due to nesting of children within parent participants, using a generalized equating equation. Thus, in these analyses, participant responses are the unit of analysis. Group membership (i.e., SES NXT group (1) vs. control group (0)) will be entered as a categorical predictor; we will also include potential covariates, including participants' gender and age, participants' baseline score on the outcome, and parental educational level, income, and depression/anxiety symptoms. Following examination of the primary outcomes, the same analyses will be conducted with respect to the secondary outcomes. For all analyses, a *p*-value of less than 0.05 will be used as the threshold for statistical significance, since this value was used as the acceptable risk of type I error in our sample size estimation (see ‘Sample size’). Additional follow-up analyses will be executed to examine whether there is a differential change over time for the two groups, as reflected in a time-by-group interaction effect and, for the intervention group, to examine differences in the outcomes based on intervention age group and number of modules completed in the intervention.

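### H10 predicts less body image dissatisfaction, but its stated outcome is an item running from too thin to too fat, with no recode or scoring direction given

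*Protocol article*

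**What the plan says.** Among the secondary hypotheses at the end of the introduction, the intervention group is predicted to report "less body image dissatisfaction (H10") at T3. The Measures section describes a single item for this: "We assessed perceptions of body size, with responses ranging from" much too thin (1) to much too fat (5). It gives the purpose of the item as "to reflect body image dissatisfaction, a potential predictor of physical and mental health". Of the somatization, body-size and sleep items together it says: "These three items serve separately as secondary outcomes".

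The Statistical analyses section fits a GEE regression on group, with the baseline score on the outcome among the covariates, and then says that "the same analyses will be conducted with respect to the secondary outcomes". The threshold is a p-value "of less than 0.05 will be used as the threshold for statistical significance".

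Nowhere does the article say that the body-size item is folded around its midpoint, dichotomised or otherwise recoded, or which direction of the score is favourable. For school absence, by contrast, it gives both the derivation and the direction: "A percentage will be calculated for full days of absence, such that higher percentages indicate higher school non-attendance".

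**The concern.** Dissatisfaction is not monotone in this score. A child rated 1 and a child rated 5 are both at the dissatisfied extreme, and the satisfied point lies between them. The two neighbouring physical-health items do not have this problem: the sleep item runs from never to almost every day, and the somatization item uses the one-directional SDQ response options. For those two, the raw code already orders children as the hypothesis needs.

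If the 1-5 code goes into the stated regression, the group coefficient answers whether one arm sees itself, or is seen, as thinner or fatter than the other. Inward moves from the two ends carry opposite signs and offset each other. H10 could then be reported as unsupported, or as pointing the wrong way, when dissatisfaction had in fact fallen. The baseline covariate would carry the same fault.

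**Working it through.** The plan gives no figure for H10, so there is nothing to reproduce. The check compares the raw item with its folded form under assumed response distributions.

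**Inputs.** From the article: codes 1 to 5 with opposite anchors, and about 700 families at 1:1, hence 700 / 2 = 350 per arm. Assumed: code 3 is the satisfied category (its label is not printed), 60% of children are there, 40% are off-centre, and the intervention moves 30% of each off-centre category one step inward.

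**Formulas.** One step inward adds 1 to the raw score of a child on the thin side and subtracts 1 on the fat side. It subtracts 1 from |score - 3| on either side. So:

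- raw change = 0.30 x (thin share - fat share)
- folded change = -0.30 x (thin share + fat share) = -0.30 x 0.40 = -0.12

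| Thin / fat share | Raw change | Folded change |
|---|---|---|
| 20% / 20% | 0.30 x 0 = 0 | -0.12 |
| 15% / 25% | 0.30 x (-0.10) = -0.03 | -0.12 |
| 10% / 30% | 0.30 x (-0.20) = -0.06 | -0.12 |
| 0% / 40% | 0.30 x (-0.40) = -0.12 | -0.12 |
| 40% / 0% | 0.30 x 0.40 = +0.12 | -0.12 |

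Swapping the two shares in any row flips the raw sign and leaves the folded change as it is.

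**Standardised size.** Take 5/15/60/15/5% in the control arm. The folded mean is 2 x 0.10 + 1 x 0.30 = 0.50, with variance 4 x 0.10 + 0.30 - 0.25 = 0.45. After the move the distribution is 3.5/12/69/12/3.5%, with folded mean 0.38 and variance 4 x 0.07 + 0.24 - 0.144 = 0.376. The pooled SD is about 0.64, so d = -0.12 / 0.64, about -0.19. The raw effect here is 0. It is about 0.04 in size at 15/25 and 0.08 at 10/30.

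**Power under a second set of assumptions.** The middle share rises from 60% to 70%, with 350 per arm, two-sided 0.05 (the article does not state sidedness), one child per family and no covariates.

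| Case | Raw difference (power) | Folded difference (power) |
|---|---|---|
| Symmetric benefit | 0 (rejects at the alpha level only) | -0.14 (83%) |
| 10% thin / 30% fat at baseline | -0.07 (24%) | -0.13 (76%) |
| 30% thin / 10% fat at baseline | +0.07 (24%) | -0.13 (76%) |
| Benefit on the fat side only | -0.12 (53%) | -0.12 (69%) |
| Benefit on the thin side only | +0.12 (53%) | -0.12 (69%) |

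Where the raw difference is positive, its power is power to find a difference in the upward direction.

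**The converse.** Compare 8/22/60/8/2% with 5/15/60/15/5%. The raw means are 2.74 and 3.00, a difference of -0.26. The folded mean is 0.50 in both, so the raw mean moves with no change in dissatisfaction.

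**The case against.** The strongest reply is that the article never says that the 1-5 code is analysed as it stands. Saying that the three items serve separately means that they are not pooled; it does not rule out a recode. The Methods section points to an online measures document and codebook that are not shown, and the item comes from an established survey. Item scoring is often left to such places. This stands as a limit on confidence. It does not remove the mismatch, because the article itself states the construct, the anchors, the item as outcome and the model, and these do not fit together without a further step.

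Three stronger readings are tempting, and the documents do not support them:

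- A reader might infer that H10 cannot be answered. The responses are collected at T1, T2 and T3, and a recode makes the hypothesis testable with the planned data.
- A reader might infer that a general shift towards too thin would be declared a success. The article gives no favourable direction for this item, and H10 speaks of dissatisfaction, not of a lower score.
- A reader might infer that the raw effect must be close to nil. That holds only when the two sides are nearly balanced. If all dissatisfaction is on one side, the raw and folded changes are equal in size.

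Parents answer for children aged 3-10 (Table 1), and one might want the main test confined to self-report at 11-17. That is a separate and debatable trade-off, and the two-ended scale does not require it.

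**Conclusion.** The mismatch is real in the text as it stands and should be corrected. A mean difference on this item is not a measure of dissatisfaction. Under the first set of assumptions, a fall of 0.12 on the folded score appears on the raw item as anything from -0.12 to +0.12, according to the baseline mix, and as exactly 0 when the two sides are balanced.

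The sizes rest on assumed response distributions, since the article gives none, and on reading code 3 as the satisfied point. The direction of the argument needs only the two opposite anchors. The effect is confined to one of twelve secondary hypotheses (H4-H15). The primary outcomes and the sample size are untouched.

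**What to change.** Define the H10 outcome as |score - 3|, range 0 to 2, higher meaning more dissatisfaction; or as off-centre versus middle category. State that the middle category is taken as the satisfied point. Apply the same recode to the T1 score used as covariate, so that outcome and baseline are on the same scale.

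The folded score keeps the difference between mild and extreme responses. The yes/no version is simpler to report but loses that difference, and the model statement would then have to say how a binary outcome is handled.

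The cost is one line of recoding and one sentence of text. No new data are needed, and no participants are lost. If the codebook already defines such a recode, one sentence in the article stating it settles the point.

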Participants also respond to questions that tap into key domains targeted by the intervention. These domains concern 1) communicating needs, 2) setting boundaries, and 3) connecting with an adult. Each domain contains three questions developed specifically for this study. The item content for domains 1) communicating needs and 3) connecting with an adult is based on the concepts of instrumental, emotional, and informational support (Taylor, 2011). For the communication needs and setting boundaries domain, the responses are rated on a 4-point scale (e.g., 0 = “No and I haven't needed help”, 1 = “No, even though I have needed help”, 2 = “Yes, one time”, and 3 = “yes, multiple times”). For the connection with an adult domain, responses are rated on a 5-point scale (ranging from 1 = ranging from “very difficult” to 5 = “very easy”). Items for each domain are averaged to create a mean score, and higher scores indicate higher frequency of communication needs, greater frequency of setting boundaries, and lower difficulty in connecting with an adult. For the communicating needs domain, participants report if they have asked for instrumental support (e.g., asked for help with money), emotional support (e.g., told someone that you are upset) and informational support (e.g., asked for advice). For the setting boundaries domain, participants are asked whether they have spoken up if parents have spoken badly about each other, have had a verbal argument in front of them, and if the parents have tried sending each other messages through them. For the connecting with an adult domain, participants are asked how easy or difficult it has been for them to seek instrumental support, emotional support, or informational support. These items were developed specifically for this study by the first and last author, and thus, no psychometric information exists for these items. These three domains serve as secondary outcomes (Hypothesis 12–14).

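### The printed 0–3 coding for communicating needs (H12) and setting boundaries (H13) mixes whether a need arose with whether the child acted, so the mean is not the frequency it is labelled as

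*Protocol article*

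**What the plan says.** The protocol article, section 1.5 (Measures), describes three domains built for this study and gives two of them the same response format: "For the communication needs and setting boundaries domain, the responses are rated on a 4-point scale". The anchors are introduced as an example, and the lower two are "0 = “No and I haven't needed help”, 1 = “No, even though I have needed help". Code 2 means the child acted once and code 3 more than once. The three items of a domain are combined without treating the lowest category separately: "Items for each domain are averaged to create a mean score, and higher scores indicate higher frequency of communication needs".

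The list of secondary hypotheses at the end of the introduction makes a higher score the predicted benefit at T3: "the intervention group will report significantly higher scores in terms of frequency of communicating needs (H12), setting boundaries (H13").

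The item content differs between the two domains. For communicating needs, "participants report if they have asked for instrumental support (e.g., asked for help with money"), with parallel items on emotional and informational support. For setting boundaries, "participants are asked whether they have spoken up if parents have spoken badly about each other, have had a verbal argument in front of them"; the third item concerns messages passed through the child. Later in the same section, on the Divorce Conflict Scale, the article says "we expect that parents may reduce their conflict in response to" the child's use of the intervention and the child's improvement.

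Table 1 gives these items to ages 6–10 (parent report) and 11–17 (self-report). Section 1.6 analyses secondary outcomes in the same way as the primary ones, at p < 0.05.

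**The concern.** One number carries two facts: whether a need arose, and whether the child acted on it. A frequency score should not separate a child who had no need from a child who had one and stayed silent, because neither acted. The printed coding puts them a point apart and ranks the silent child in need higher. That is the wrong order if higher means better, and it is also wrong if the score only means frequency.

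For setting boundaries there is a second problem. Each item presupposes conflict behaviour by the parents. If that behaviour stops, the natural answer becomes the lowest code, and the item loses one, two or three points on a scale that H13 predicts will rise. The article itself names reduced conflict as a possible effect of the intervention.

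At stake is the reading of two secondary results. A difference in either direction could reflect a change in need, a change in behaviour, or both. The planned adjustment for the baseline score does not remove this, because the change in need comes after randomisation.

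**Working it through.** The article gives no figure for these outcomes, so there is none to reproduce. The check is on the direction of the score. The codes come from section 1.5; every response share below is an assumption.

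**1. Ordering (H12 and H13).** Change in item score for each move:
- no need to unmet need: 1 − 0 = +1, with no change in action;
- unmet need to no need: 0 − 1 = −1, with no change in action;
- acted once to no need: 0 − 2 = −2;
- acted several times to no need: 0 − 3 = −3.

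The first two moves show the mislabelling without any assumption about conflict. If 20% of children moved from no need to unmet need and nobody acted more, the item mean would rise by 0.20 × 1 = 0.20 towards the hypothesis.

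**2. Falling need (direct for H13).** Suppose children in need answer 30% no, 30% once and 40% several times in both arms.
- Mean in need: 0.3 × 1 + 0.3 × 2 + 0.4 × 3 = 2.1.
- Control, need 70%: 0.7 × 2.1 = 1.47.
- Intervention, need 50%: 0.5 × 2.1 = 1.05.
- Difference: −0.42 on the 0–3 scale. Unmet need goes from 0.7 × 0.3 = 21% to 0.5 × 0.3 = 15%.

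**3. How much speaking up would offset it.** Let q be the probability of need, s the probability of acting when needed, and m the probability of acting several times given action. The item mean is E = q[(1 − s) × 1 + s((1 − m) × 2 + m × 3)].
- Control, q = 0.60, s = 0.50, m = 0.50: E = 0.60 × 1.75 = 1.05.
- q = 0.45, s unchanged: 0.45 × 1.75 = 0.79, difference −0.26.
- q = 0.45, s = 0.70: 0.45 × 2.05 = 0.92, difference −0.13.
- Break-even s = (1.05/q − 1)/1.5: 0.61 at q = 0.55, 0.73 at q = 0.50, 0.89 at q = 0.45. At q = 0.40 it is 1.08, so no value of s is enough.

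**4. A case with the opposite sign.** If need falls only from 70% to 65% and answers among those in need move from 30/30/40 to 15/35/50, the mean in need is 0.15 + 0.70 + 1.50 = 2.35. The score is 0.65 × 2.35 = 1.53 against 1.47, in favour of H13.

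**5. Effect of recoding 0, 0, 1, 2.** The moves between no need and unmet need now change the score by 0. In the example of step 2 the mean in need is 0.3 × 1 + 0.4 × 2 = 1.1, so the arms have 0.77 and 0.55, difference −0.22 on a 0–2 scale. The label is then correct, but the score still falls when need falls.

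**The case against.** A reader might infer that reduced conflict would make both hypotheses come out reversed and that a null or negative result would be uninterpretable. The documents do not support that, for four reasons.

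- The conflict route does not reach H12 directly. Its items concern help with money, being upset and advice, and nothing in the article predicts less need for such help.
- For H13 the article says only that conflict may fall. The intervention also trains the competing behaviour, with a module on saying yes and no, and step 4 shows a net result in the predicted direction.
- The Divorce Conflict Scale is collected at all three time points from parents and from youths aged 11–17, so a fall in conflict would be visible beside H13.
- The printed anchors follow an e.g. and are worded for help-seeking. The exact boundaries wording is in the measures document and codebook on the Open Science Framework, which is not at hand.

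These objections stand, and they limit the point. They do not remove it: the article assigns the 4-point scale to both domains, prints the order of codes 0 and 1, averages the items and calls the result frequency. This is a stated scoring rule, not a detail left to an analysis plan.

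A reader might also infer that H12 and H13 should be tested on unmet need instead. That changes the construct. In step 2 unmet need improves from 21% to 15% although children in need behave identically in both arms. It can also mislead the other way: if need rises from 50% to 70% and failure to act falls from 30% to 25%, unmet need rises from 15% to 17.5% while acting rises from 35% to 52.5%. It would not cover all randomised children either, since ages 3–5 are not asked.

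**Conclusion.** The point holds in limited form. For both domains the printed codes make the mean something other than frequency: two zero-frequency answers differ by one point per item, and unmet need outranks no need. This follows from the article's own wording.

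For H13 a fall in parental conflict also pulls the score against the hypothesis, by 0.42 or 0.26 in the two assumed examples where behaviour in need is unchanged. The net sign depends on how far speaking up increases, and the claim assumes that the boundaries anchors parallel the printed ones. For H12 only the ordering fault is established.

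These are two of the twelve secondary hypotheses. H1–H3 and the sample size, which was set on H1, are unaffected. The article acknowledges that the items have no psychometric information, so no validation supports the present ordering. It should be corrected before the outcomes are analysed.

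**What to change.** 1. Score both No answers as zero and the two Yes answers as 1 and 2 (0, 0, 1, 2), then average as planned. Apply the same recode to the baseline score used as covariate. H12 and H13 keep their wording and direction.
2. Report by arm, among the children asked these items (ages 6–17), the share with any need and the share with unmet need, that is, those answering "No, even though I have needed help" or its boundaries equivalent.
3. Give action among items with a need as supportive only, because it conditions on an event after randomisation.
4. Interpret H13 beside these shares and the Divorce Conflict Scale. Confirm the boundaries anchors against the codebook first.

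The cost is a recode of items already collected and a few extra descriptive results. The recoded frequency still falls when need falls (0.77 to 0.55 in the example), so need must be reported beside it.
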